### Inclusion and exclusion criteria

2.4

The pretest risk of lung cancer is dependent especially on the smoking duration, age, sex, family history of lung cancer.^[12,13]^ The inclusion criteria should define a population of participants with the highest risk of lung cancer who are capable of undergoing curative treatment if cancer is found. The recommended threshold by the UK Lung Cancer Screening Trial was based on the prediction result of at least 5% risk of developing lung cancer in the following 5 years.^[12]^

The highest incidence of lung cancer in the Czech Republic is between 60 to 79 years (Fig. 1).^[1]^ The lung screening trials with the highest sample sizes included patients aged approximately between 55 and 75 years of age.^[14]^ The CHEST Guideline and Expert Panel Report recommend the optimal screening 55 to 77 years.^[15]^ The U.S. Preventive Services Task Force recommends annual screening up to 80 years of age, while the Centers for Medicare & Medicaid Services (CMS) end coverage at the age of 77, corresponding to the oldest age at the time of the final annual screen in the NLST. The optimal age span for screening was set to 55 to 74 years to precede the diagnosis of advanced lung cancer and to take into account a shorter life expectancy in the Czech Republic. The male gender carries a higher risk of lung cancer by a factor of 1.5 to 2.^[16]^ This fact is related to a smaller proportion of women, who are heavy smokers and can therefore be equalized by the pack-years inclusion criterion.

**Figure 1 F1:**
[figure not shown]
Incidence rate of C34 (Malignant neoplasm of bronchus and lung) by age in 2017 in the Czech Republic. Data from the National Oncology Registry.^[1]^

The best predictor of lung cancer is smoking duration and intensity. It is expressed as the number of cigarettes per day for a given number of years (“pack years”, 1 pack = 20 cigarettes, 1 pack-year = 20 cigarettes daily for 1 year). Various thresholds have been used with a range from 15 pack-years up to 30 pack-years.^[14,15,17]^ Greater risk means better efficacy of screening. The pause from becoming a non-smoker was determined between 10 and 15 years in various studies, for it is known that after this period the risk of developing lung cancer decreases. The recommendations of the CHEST Guideline and Expert Panel Report recommend a threshold of 30 pack-years and <15 years from the cessation of smoking.^[15,18]^

Further risk factors include obstruction on spirometry (FEV-1 below 70% has OR 2.9), which is a criterion that would be difficult to implement.^[19]^ Moreover, patients with greater obstruction have lower vital capacity limits and higher perioperative risk if resection would be considered.

Patients who are not amenable to curative treatment due to their poor performance status are unlikely to benefit from the early detection of lung cancer. The performance of the patients can be assessed by their ability to undergo physical exertion such as climbing the stairs. In the DLCST trial, the threshold was the ability to climb 36 steps without pause.^[20]^ We define good performance status as the ability to climb stairs at least 1 floor without any difficulty or pause.

#### Inclusion criteria

2.4.1

Age 55 to 74 yearsSmoking: ≥30 pack-years, smoker or ex-smoker <15 yearsPerformance status (0–1) – can climb at least 1 floor without any difficulty or pause

#### Exclusion criteria

2.4.2

Body weight above 140 kgMalignant disease within the last 10 years (except non-melanoma skin cancer).Chest CT less than 1 year ago, chest x-ray ≤6 months agoClinical signs suspicious of lung cancer (weight loss, new cough, hemoptysis)Recent (≤2 months) bronchopneumonia, pneumonia

### Screening interval

2.5

The selection of the optimal screening interval, which can be obtained by processing the NELSON study data, is important as well. It appears that the extension of the screening interval (in the NELSON trial it was 1 year, 2 years, and 2.5 years) brings a stationary incidence of diagnosed tumors to a screening round (0.8%), but worsening of the average stage of newly diagnosed tumors in the last round of screening (i.e., 2.5 years).^[21]^ Thus, the 2.5-year interval was too long. The screening interval was set at 12 months.

### Low-dose CT (LDCT)

2.6

The CT settings for screening protocols varied between 80 and 140 kVp with a minimum of 20 mAs tube time-current product.^[15]^ The reported effective doses ranged from <0.4 mSv in lean patients to 2mSv. More recent trials adopted automated kV selection and mAs modulation based on the attenuation profile of the patient. Sufficient image quality and diagnostic performance of ultra-low-dose protocols (<0.2 mSv) for the detection of pulmonary nodules and even ground-glass lesions with the use of model-based iterative reconstruction technique has been confirmed in phantom and clinical studies.^[22,23]^ For a standard-size patient, this corresponds to a CTDIvol <0.6 mGy for a 25 cm scan.^[13,18]^

#### CT acquisition protocol

2.6.1

≥64 slice scannerAxial and longitudinal current modulationIterative reconstruction – hybrid or model-basedTube voltage: 80–120 kV – automated selection (auto kV)Tube current: ref. 10 mAs (automated modulation) – target CTDIvol≤0.6 mGy (standard-size patient), effective dose ≤0.2 mSvExtent: lung apices – costophrenic anglesCommand: “Take a deep breath and hold it”.

#### Image reconstruction

2.6.2

Isotropic (≤1 mm), soft tissue (Body kernels [B, Bf, Br, BI] 20–42 for Siemens or equivalent), contiguous or overlapped, axial plane, iterative reconstruction (hybrid, model-based), and

-5 mm axial contiguous-5 mm coronal contiguous-5 mm sagittal contiguous

≤1 mm volumetric isotropic (≤1 mm), soft tissue (Body kernels [B, Bf, Br, BI] 50–70 for Siemens or equivalent), contiguous or overlapped, axial plane, iterative reconstruction (hybrid, model-based) optional, and

-1.5 mm axial contiguous

### Interpretation of LDCT

2.7

The interpretation of CT findings is based on the probability that a lesion harbors malignity and how fast it can develop beyond the localized stage. Several academic groups including the Fleischner society, the British thoracic society, the American College of Chest Physicians have proposed guidelines on the management of pulmonary nodules. They derive the risk and the need for further management from the imaging features of the nodule (size or volume, spiculation, upper lobe location, perifissural location), the lungs (emphysema), and the pretest probability of malignancy (age, family history of malignancy, obstruction).^[24,25]^

The best predictor of malignancy of a solid nodule is its size and growth rate.^[26]^ From a mean diameter of 6 mm it starts to increase steadily.^[27]^ The prevalence of malignancy in nodule <5 mm is extremely low, about half a percent.^[28]^ In the NELSON trial, the risk of malignancy in subjects with nodules <100 mm^3^ was similar to those without nodules.^[29]^ Based on these data, the lower size threshold for nodules that require follow up was increased to 6 mm or 100 mm^3^ in the Fleischner society guidelines^[6]^ and 5 mm or 80 mm^3^ in the BTS guidelines.^[30]^

The NELSON study showed that small nodules (<100 mm^3^) are not predictive for lung cancer and that nodules ≥300 mm^3^ or ≥10 mm require timely attention.^[29]^ Malignant nodules showed an exponential growth and nodule doubling time with a threshold of 600 days was suggested as the most optimal for nodules sized between 100 and 300 mm^3^.^[31]^

There is little information about the behavior of subsolid nodules. Ground-glass nodules show very slow growth, beyond the 600 days VDT threshold, and are safe to follow-up on an annual basis.^[6]^ In part-solid nodules, the size of its solid component and its growth are predictive of lung cancer.

The annual incident rates of new nodules (ELCAP, I-ELCAP, PLuSS, and Mayo trials) are reported between 3.4 and 13%. These new nodules are logically fast-growing and the data we have available show that the probability of malignancy in such a newly emerging nodule is 1.6% to 7.5%. Therefore, it may be necessary to choose a lower volume limit for these new nodules than for the first round of screening.^[31]^ The models that aim to distinguish between malignant and benign nodules include the model of McWilliams and the American College of Radiology model, which in 2014 published its Lung-RADS assessment criteria, which were updated in 2019 (Lung-RADS 1.1).^[7]^ The Lung-RADS model is the most cited as it is used in virtually all U.S. screening centers. It includes 5 categories that determine the type of lesion and its subsequent management based on the type of the lesion, its size, and behavior.

About half of the asymptomatic high-risk individuals undergoing screening by LDCT present with more than 1 nodule. At baseline, in the NELSON trial, where the management was based on the largest or most suspicious nodule, malignancy was detected mostly in the largest nodule (97%).^[31]^ However, in the PanCan study, one-fifth of the positive individuals were diagnosed with cancer in a lesion that was not the largest.^[27]^

### Evaluation and management of pulmonary nodules

2.8

In this study, the nodules will be assessed in Intellispace Portal (current version 10) Lung analysis package. This package performs automated detection of nodules and automatic segmentation of their volume with manual adjustment by the radiologist, where necessary. Nodules that would escape automatic detection will be segmented manually (lung window) - the agreement between manual and automated segmentation is reported to be excellent.^[24]^ In lesions, where volume segmentation would be difficult or unreliable (e.g., perihilar), the effective diameter will be used (the average of 2 maximal perpendicular diameters), with the exception of broad-based subpleural lesions, where short diameter will be used instead. In non-solid nodules, the ground-glass part will be measured by effective diameter regardless of segmentation.

The management will be based on the largest or most suspicious nodule. Nodules 70 mm^3^ and larger will be recorded and their doubling time calculated if they would be found in the previous scan, wherever available. A nodule is by definition a rounded (spherical, oval) circumscribed focus of abnormal tissue.

The proposed management protocol uses the recursive definition of nodules (with regard to their growth). It is based on the recommendations of the American College of Radiology (ACR), The Fleischner society guidelines, and results of the NELSON trial.^[32,33]^ The primary assessment of risk (that a lesion harbors malignity) is based on volumetry and doubling time (Tables 1–3). For solid nodules, the volume threshold is 100 mm^3^ (70 mm^3^ for new nodules), the VDT threshold is 600 days. Subsolid nodules are rare (0.7%) and the risk of malignancy or premalignancy is low (6%) unless a new solid component appears.^[34,35]^ The data on the management of sub-solid nodules are scarce which is reflected in the diversity of recommendations across different guidelines.^[36]^ The update of the Lung-RADS model in 2019 increased the lower boundary for purely ground-glass nodules that require further management to 30 mm.^[7]^

**Table 1 T1:** Management of solid nodules.

SOLID NODULES				
Description	Findings	Management	Risk	Estimated prevalence
1 - Benign appearance or behavior	• normal or benign findings^∗^	→1 year round	<1%	90%
	• perifissural nodule <9.8 mm (<500 mm^3^)^∗∗^			
	• <100 mm^3^ (<5.8 mm)			
	• new <70 mm^3^ (<5.1 mm)			
	• nodules with VDT >600 days			
	• benign histology, PET/CT negative			
2 - Low risk	• ≥100 to <300 mm^3^ (≥5.8 to <8.3 mm)	• 5 month LDCT	1%–6%	8%
	• new ≥70 to <100 mm^3^ (≥5.1 mm to <5.8 mm)			
3 - Intermediate risk	• ≥300 to <750 mm^3^ (≥8.3 to <11.2 mm)	• 3 month LDCT	9%–11%	2%
	• growing ≥100 to <300 mm^3^ (≥5.8 to <8.3 mm)	• optional *PET/CT* if ≥300 mm^3^ (≥8.3 mm)		
	• new ≥5.8 to <8.3 mm (≥100 to <300 mm^3^)			
	• endobronchial nodule			
4 - High risk	• ≥11.3 mm (≥750 mm^3^)	• PET/CT	19%–26%	1%
	• new or growing, and ≥ 8.3 mm (≥300 mm^3^)	• Tissue sampling^∗∗∗^		
	• other features suggesting malignancy (spiculation)	• Contrast-enhanced CT of thorax		
		• Equivocal appearance of a benign finding: 1–2 month LDCT		

**Table 2 T2:** Management of part-solid nodules.

PART-SOLID NODULES		
Description	Findings	Management
1 - Benign appearance or behavior	• <8.3 mm total diameter (<300 mm^3^)	→ 1 year round
	• solid part VDT>600d	
	• benign histology, PET/CT negative	
2 - Low risk	• ≥8.3 mm total diameter (≥ 300 mm^3^) and solid part <100 mm^3^ (<5.8 mm)	• 5 month LDCT
	• new ≥5.1 to <8.3 mm total diameter (≥70 to >300 mm^3^)	
3 - Intermediate risk	• ≥8.3 mm (≥300 mm^3^) and	• 3 month LDCT
	a] solid part ≥100 to <300 mm^3^ (≥5.8 to <8.3 mm)	• optional PET/CT if solid part ≥300 mm^3^
	b] new or growing solid part <70 mm^3^ (<5.1 mm)	(≥ 8.3 mm)
4 - High risk	• solid part ≥300 mm^3^ (≥8.3 mm)	• PET/CT
	• new or growing solid component >70 mm^3^ (>5.1 mm)	• Tissue sampling^∗^
	• other features suggesting malignancy	• Contrast-enhanced CT of thorax
		• Equivocal appearance of a benign finding:
		1–2 month LDCT

**Table 3 T3:** Management of non-solid nodules.

NON-SOLID NODULES		
Description	Findings	Management
1 - Benign appearance or behavior	• <30 mm diameter (<14000 mm^3^)	→ 1 year round
	• ≥30 mm diameter (≥14000 mm^3^) and stable	
2 - Low risk	• <30 mm diameter (≥14000 mm^3^) and growing	• 5 month LDCT
	• ≥30 mm diameter (≥ 14000 mm^3^)	
3 - Intermediate risk	–	–
4 - High risk	• ≥30 mm diameter (≥14000 mm^3^) and growing >1.5 mm / VDT<600 days	• PET/CT
	• other features suggesting malignancy	• Tissue sampling^∗^
		• Equivocal appearance of a benign
		finding: 1–2 month LDCT

Volume doubling time (VDT) based on volume (V) measurements:

VDT = [ln2 ∗ (T1 – T0)] / [ln (V1/V0)]

Volume doubling time based on mean diameter (D) measurements:

VDT = [ln2 ∗ (T1 – T0)] / [3 ∗ ln (D1/D0)].

Where T1 and T0 are timepoints of the measurement.

A positive screening test is defined as a high risk finding or intermediate risk finding where verification (PET/CT, tissue sampling, contrast-enhanced CT) was requested. An indeterminate test is defined as low and intermediate risk finding, further managed by LDCT. A negative test (benign appearance or behavior) does not mean that an individual does not have lung cancer.

Secondary findings will be reported as incidental findings and categorized according to their expected clinical significance as shown in Table 4.

**Table 4 T4:** Classification of secondary findings.

SECONDARY FINDINGS	
	Description
1	Normal exam with regard to patient's age, benign variants, clinically unimportant findings
	- e.g., lobus v. azygos, degenerative spine disease, vertebral hemangioma
2	Potentially important findings
	- e.g., pleural effusion, pericardial effusion (>10mm), pulmonary fibrosis, mediastinal lymphadenopathy, pneumonia, emphysema, vertebral compression, aortic aneurysm

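### Tables 2 and 3 contain overlapping or misprinted rows for subsolid nodules, so that a small growing nodule fits both the benign category and a higher one

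*Protocol article*

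**What the plan says.** All the rows in question are in section 2.8 of the protocol article.

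- **Table 2, benign category:** "<8.3 mm total diameter (<300 mm^3", followed up at the annual round. The row has no condition on the solid part.
- **Table 2, high risk:** "new or growing solid component >70 mm^3^ (>5.1 mm", sent to PET/CT, tissue sampling or contrast-enhanced CT. The row has no minimum total size.
- **Table 3, benign category:** "<30 mm diameter (<14000 mm^3", followed up at the annual round. The row does not require absence of growth.
- **Table 3, low risk:** "<30 mm diameter (≥14000 mm^3^) and growing", sent to 5-month LDCT.
- **Table 3, high risk:** at 30 mm and above, "growing >1.5 mm / VDT<600 days".

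The text shows the intent. Section 2.7 says: "In part-solid nodules, the size of its solid component and its growth are predictive of lung cancer". Section 2.8 says of subsolid nodules that "the risk of malignancy or premalignancy is low (6%) unless a new solid component appears". On measurement, section 2.8 says: "In non-solid nodules, the ground-glass part will be measured by effective diameter regardless of segmentation".

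Section 2.8 also ties the category to the test result. Benign is negative, high risk is positive, and low risk managed by LDCT is indeterminate.

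**The concern.** A decision table should give one answer for one nodule. Two rows of Table 2 give opposite answers for a small part-solid nodule whose solid part is new or growing and exceeds 70 mm³. A reader who stops at the size row reports a negative test and books the annual round. A reader who goes on to the growth row reports a positive test and starts a diagnostic work-up. The first reading is the less safe one.

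Table 3 has a milder form of the same problem. A growing ground-glass nodule below 30 mm satisfies the benign row (annual round, negative) and, once the sign is read sensibly, the low-risk row (5-month LDCT, indeterminate).

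At stake are the management of individual participants, the counts of negative, indeterminate and positive tests, and the second secondary objective (number, cost and complications of further examinations, section 2.2.2).

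**Working it through.** **1. The tables' own conversions.** With sphere volume V = (π/6)·d³:

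- 5.1 mm gives 69.5 mm³ (printed 70)
- 5.8 mm gives 102.2 mm³ (printed 100)
- 8.3 mm gives 299.4 mm³ (printed 300)
- 30 mm gives 14,137 mm³ (printed 14,000)

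All agree within 3%, so diameter and volume are meant as equivalents.

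**2. Table 2 applied literally.** Each example has a growing solid part.

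| Total (mm³) | Solid part (mm³) | Categories met |
|---|---|---|
| 250 | 60 | 1 |
| 250 | 71 | 1 and 4 |
| 250 | 100 | 1 and 4 |
| 299 | 150 | 1 and 4 |

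The conflict needs a solid part above 70 mm³ (5.1 mm) inside a nodule below 300 mm³ (8.3 mm). That is physically possible, but the range is narrow.

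For growth from 40 to 80 mm³ in 365 days, the article's volume formula gives VDT = ln 2 × 365 / ln(80/40) = 365 days, well inside the 600-day threshold. If growing means VDT below 600 days (an assumption), the solid part must grow by a factor of more than 2^(365/600) = 1.52 in a year, or 2^(152/600) = 1.19 in five months.

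A new part-solid nodule of 70 to below 300 mm³ total likewise meets both the benign size row and the low-risk row for new nodules. That low-risk row also has a reversed sign at its upper limit of 300 mm³.

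**3. Table 3, low-risk row.** The diameter for 14,000 mm³ is (6 × 14,000/π)^(1/3) = 29.90 mm. Taken literally, the row holds only nodules from 29.90 mm to just under 30 mm, a band of 0.1 mm. The other rows of Table 3 pair below 30 mm with below 14,000 mm³, so the sign is a misprint. Correcting it leaves the overlap with the benign row, because that row does not exclude growth.

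**4. Table 3, the slash in the high-risk row.** The diameter formula is VDT = ln 2 × T / [3 ln(D1/D0)], with D0 = 30 mm.

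- Growth of 1.5 mm over 152 days: VDT = ln 2 × 152 / [3 ln(31.5/30)] = 720 days.
- Growth needed for VDT = 600 days at 152 days: 30 × (2^(152/1800) − 1) = 1.8 mm.
- The two criteria coincide at T = 1800 × log₂(31.5/30) = 127 days.

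At the 5-month scan, then, reading the slash as *or* needs 1.5 mm and reading it as *and* needs about 1.8 mm.

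**5. Number affected.** The article calls subsolid nodules rare, at 0.7%, without naming the unit. If that is per participant (an assumption), the count is 0.007 × 2,500 = 17.5, or 0.007 × 2,250 = 15.75 at 90% adherence. If it is per nodule, the count scales with the mean number of nodules per participant, which is not given; each further nodule per participant would add another 16 to 18. Either way, only an unknown part falls in the rows above.

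**The case against.** The strongest defence is that these tables are built throughout as a plain size row plus rows qualified by behaviour on follow-up. Table 1 has the same literal overlaps: a solid nodule of 100 to 300 mm³ is low risk by size and intermediate risk if growing. Section 2.8 describes the scheme as recursive with regard to growth, and its text states a solid-nodule threshold of 100 mm³ with 70 mm³ for new ones. A careful reader can infer that the qualified row prevails. High risk also has a catch-all for other features suggesting malignancy.

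Most of this stands, and it keeps the point minor. But the precedence is nowhere stated. The rule on the largest or most suspicious nodule chooses between nodules, not between categories for one nodule. Nor can a reader simply take the highest category: that would cancel the Table 3 row that returns stable nodules of 30 mm or more to the annual round.

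The sign in Table 3 does little harm by itself, since ground-glass is sized by diameter.

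A condensed article may omit detail, and footnote text is not available here. The rows are nevertheless printed in full, and the only footnote marker in Tables 2 and 3 is on tissue sampling. An unmarked legend cannot be excluded.

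**Conclusion.** The point holds as a minor one. Applied literally, the benign rows of Tables 2 and 3 give a less safe answer for growing subsolid nodules than sections 2.7 and 2.8 intend, and one Table 3 row has a reversed sign. The number of participants affected is small and not given by the protocol; 16 to 18 per round is a ceiling only if the 0.7% is per participant.

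A reader might infer more than this from the same rows, without support in the article:

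- *The primary result is compromised.* The primary objective counts cancers by stage and does not use the nodule category. The article also gives no sign that anyone was managed wrongly.
- *The slash makes a large difference.* Over 365 days the two readings do separate, to 1.5 mm against 30 × (2^(365/1800) − 1) = 4.5 mm. But Table 3 sends a nodule of 30 mm or more to a 5-month scan first, where the gap is about 0.3 mm. The slash needs clarifying; it is not a serious fault.
- *The rows for VDT above 600 days contradict the size rows.* Those rows have a purpose only if follow-up behaviour overrides size, so they are probably settled. A confirming sentence is enough.

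**What to change.** Change the wording as follows.

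- **Table 2, benign size row:** *total below 300 mm³, not new at 70 mm³ or more, and without a solid part above 70 mm³ that is new or growing*.
- **Table 2, low risk, new nodules:** reverse the sign so that the upper limit is below 300 mm³.
- **Table 3, low risk:** below 30 mm, with below 14,000 mm³ in the parenthesis, and growing.
- **Table 3, benign row:** below 30 mm and not growing.
- **One sentence for Tables 1 to 3:** a row qualified by new, growing or stable overrides the plain size row; if two such rows are met, the higher category applies.

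Three clarifications can be made at the same time: replace the slash in Table 3 with *or* or *and*, as the investigators decide; confirm that VDT above 600 days overrides the size category, and whether this also holds at 750 mm³ and above; and use one diameter for 750 mm³ in Table 1, where 11.2 and 11.3 mm both appear (the sphere formula gives 11.27 mm).

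The cost is low: a few cells, one or two sentences, notice to the registry and ethics committee, and a recheck of any subsolid nodules with a prior scan that fall in the corrected rows.
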